**Statistical Analysis Plan**

**1. General Principles**

All primary analyses will be conducted following the Intention-to-Treat (ITT) principle. All participants will be analyzed in the groups to which they were originally assigned, regardless of the level of intervention completion or dosage received.

Unless otherwise specified, a p-value of < 0.05 will be considered statistically significant for all analyses.

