**3. Intervention Effect Estimation**

The primary evaluation of intervention effects will be conducted at the post-intervention timepoint (T1).

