**3.1 Continuous Outcomes**

Continuous outcomes will be analyzed using multilevel linear regression models.

- **Model Specification:**
  - **Random Effects:** Participant ID nested within cluster.
  - **Fixed Effects:** Group (intervention vs. control), time (T0, T1, T2, T3), and the group × time interaction term. The intervention effect will be determined by the interaction term.

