**6. Causal Effect Among Compliers**

The Complier Average Causal Effect (CACE) will be estimated using a two-stage instrumental variable (IV) approach, with random assignment serving as the instrument for compliance.

- **Stage 1:** Compliance status (defined as completing at least 30 chatbot modules) will be regressed on the randomization variable to generate predicted compliance probabilities for each participant.
- **Stage 2:** Each outcome will be modelled as a function of the predicted compliance indicator from Stage 1. This stage will use mixed-effects regression models with random intercepts at both the cluster and participant levels to account for data clustering and repeated measures.
  - Continuous outcomes will be analyzed using linear mixed-effects models.
  - Count outcomes will be analyzed using Poisson or negative binomial mixed-effects models, as appropriate.

This two-stage IV framework is designed to provide an unbiased estimate of the causal effect of the intervention among compliers, addressing non-adherence while preserving the benefits of randomization.

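### The T1 mixed models recover the all-assigned effect only if loss before T1 is unrelated to chatbot use; an analysis using module completion should be added, and the CACE sample fixed

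*SAP*

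**What the plan says.** SAP Section 1 sets the target of the primary analysis: everyone is analysed in the assigned group, "regardless of the level of intervention completion or dosage received". Section 3 places the primary evaluation at T1.

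Section 3.1 gives the fixed effects as "Group (intervention vs. control), time (T0, T1, T2, T3), and the group × time interaction term", with the random effect "Participant ID nested within cluster", and adds: "The intervention effect will be determined by the interaction term". Section 3.2 carries the same structure over to the Poisson or negative binomial models for frequency outcomes.

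The only sensitivity analysis, in Section 3.3, adds child and caregiver age and gender. Module completion appears only in Section 6, where compliance means at least 30 chatbot modules and Stage 1 is fitted "to generate predicted compliance probabilities for each participant". Section 7 presents the SAP as the document that fixes the models and methods exactly.

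**The concern.** A likelihood-based mixed model has to make some implicit prediction for a caregiver with a T0 score but no T1 score. Here the prediction rests on arm, cluster and the caregiver's own other scores. How much of the chatbot was used is not in the model, although it arises after baseline and could affect both the outcome and the chance of being assessed.

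If low users are lost more often and benefit less, their missing outcomes are filled in effect from a group that used the programme more. The estimate then moves from the effect in everyone assigned towards the effect in those still assessed. The age and gender adjustment in Section 3.3 would not reveal this. The one variable that could, module completion, must be collected for Section 6 anyway. A related question arises for the CACE if its two stages use different sets of participants.

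**Working it through.** The SAP states no attrition, compliance or effect figure, so there is nothing of its own to reproduce. All rates and effects below are assumptions, in SD units.

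**What the model implies for a lost caregiver.** With a saturated group × time model and within-person correlation ρ, a caregiver with T0 only has the implied T1 value

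arm T1 mean + ρ × (own T0 score − arm T0 mean),

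leaving the cluster term aside. Averaged over lost caregivers with typical baselines, this is the mean gain of assessed members of the same arm. Conditioning on baseline does not repair loss driven by later use.

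**Size by compliance.** Assume 50% compliers, an effect of 0.40 in compliers and 0 in others, no prognostic difference between them, and uninformative control-arm loss. The true all-assigned effect is 0.50 × 0.40 = 0.20. With T1 assessment rates r_c (compliers) and r_n (others):

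share of compliers among assessed = 0.5 r_c / (0.5 r_c + 0.5 r_n); expected estimate = share × 0.40.

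| r_c / r_n | Share | Expected estimate | Overstatement |
|---|---|---|---|
| 90% / 60% | 0.45/0.75 = 0.600 | 0.240 | 20% |
| 95% / 65% | 0.475/0.80 = 0.594 | 0.237 | 19% |
| 90% / 75% | 0.45/0.825 = 0.545 | 0.218 | 9% |

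A simulation used 10,000 replicates, 300 per arm, correlation 0.5, 85% of controls assessed and no clustering. The model gave 0.241, 0.238 and 0.217. Imputing T1 from T0 and module completion gave 0.201, 0.200 and 0.199 (Monte Carlo SE 0.001). A separate run found almost no loss of precision from adding module completion (SE 0.089 versus 0.090).

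**Check with clustering.** Let d₁ be the loss in the intervention arm, e_r the effect in those retained and e_l the effect in those lost. Then bias = d₁ × (e_r − e_l). With e_r = 0.30 and e_l = 0:

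- 10% loss: true effect 0.27, bias 0.03 (0.03/0.27 = 11%)
- 20% loss: true effect 0.24, bias 0.06 (0.06/0.24 = 25%)
- 30% loss: true effect 0.21, bias 0.09 (0.09/0.21 = 43%)

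This was simulated with 21 clusters (SAP Section 2) of 28, a size within the SAP's 20–35, and ICC 0.03, within its 0.01–0.05. With T0–T1 data the model gave 0.295, 0.294 and 0.307; with T0–T3 data 0.312, 0.300 and 0.304 (Monte Carlo SE 0.005–0.006). Lost families stayed lost in this simulation, so using the later waves did not help.

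**Direction.** Let d₀ be the control-arm loss and c the difference in change between lost and retained controls. Then bias = d₁(e_r − e_l) + d₀c. With 20% loss in both arms, e_r = 0.30 and e_l = 0:

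- c = 0: 0.06
- c = −0.30: 0.06 − 0.06 = 0
- c = +0.30: 0.06 + 0.06 = 0.12

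If lost intervention families gained 0.40 and c = 0, bias = 0.2 × (0.30 − 0.40) = −0.02. With 10% intervention loss, 30% control loss, e_l = 0 and c = −0.30, it is 0.03 − 0.09 = −0.06. With no effect in anyone, the simulated estimate was 0.009, within noise of zero.

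**CACE at 90%/60%.** With Stage 1 on all assigned and the outcome contrast effectively from those assessed: 0.24/0.50 = 0.48. With both on those assessed: 0.24/0.60 = 0.40, the assumed complier effect. Simulation gave 0.486 and 0.405.

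**The case against.** The strongest reply is that nothing in the SAP shows loss to be tied to use. Section 2 places the programme inside the preschool's ordinary support for parents, with access to every family there, so contact for assessment may not depend on the chatbot at all. The method of assessment is not stated. The protocol, which is not at hand, may also deal with missing outcomes. This stands as far as it goes: the link is an assumption, and the point concerns how the stated models fit the stated target, not a missing paragraph.

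A reader might infer that the Section 1 sentence is itself wrong. It is not: analysing people as assigned is sound, and the sentence makes no claim about missing outcomes. A reader might also infer that the bias must favour the intervention and arise in one arm only. The control-loss calculations show that it can vanish or reverse.

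The size is modest too. The illustrated biases of 0.018 to 0.04 SD are about 0.2 to 0.4 of a standard error (0.018/0.09 and 0.04/0.09). Where nobody benefits, this mechanism alone produces no false positive.

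Finally, imputing from modules still assumes that lost low users resemble assessed low users. That is correct, and is why a further check is worth having. None of this removes the case for an inexpensive analysis that would show whether the condition matters.

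**Conclusion.** The point holds conditionally. The models in Sections 3.1 and 3.2 deliver the Section 1 effect at T1 only if loss is unrelated to chatbot use once arm, cluster and the participant's other scores are taken into account. Overstatement needs three things together: low users are lost more often, they gain less, and control-arm loss is uninformative. Under the 50%-complier assumptions it is about 9% to 20%. In the harsher illustration, where every lost family gained nothing, it is 11% to 43% for losses of 10% to 30%. The documents cannot say which applies, if either.

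It is tempting to add that the CACE is inflated by the same factor. Section 6 does not support that as fact. Its wording on Stage 1 leans towards all participants, but it does not fix the sample for either stage, and the inflation disappears when both use the same assessed set. What is established is an ambiguity that should be settled.

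**What to change.** **Section 3.3.** Keep the covariate-adjusted analysis, which answers a separate question, and add a missing-outcome analysis of the T1 comparison for all assigned participants:

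- Multiply impute missing T1 scores by arm from the T0 score, cluster and, in the intervention arm, modules completed by T1. Then refit the Section 3.1 and 3.2 T1 comparisons.
- Report T1 loss by arm and, in the intervention arm, by module completion.
- Ideally include a delta or reference-based check, because imputing from modules corrects only loss that module use explains.

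**Section 6.** State that both CACE stages use the same participants: either all assigned with imputed outcomes, or the same assessed set.

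The cost is a few lines of SAP text and an imputation programme using module data that Section 6 already requires. The downside is more analysis work and a possibly smaller reported effect.

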**2. Sample Size and Power Calculation**

As this is a pragmatic trial, the sample size is primarily determined by real-world logistical constraints. While initial estimates suggested access to approximately 79 participants per group, the decision to further embed the intervention into the routine parenting support offered by the preschool allowed us to access all families within the setting.

To maximize the available sample, based on recruitment capacity, power calculations will assume 21 clusters, each comprising 20–35 participants (four discrete values), and intra-cluster correlation coefficients (ICCs) ranging from 0.01 to 0.05 (five values).

Prior to implementation, power calculations will be conducted to estimate the minimum detectable effect size (MDES) for the primary outcome, for opportunities for early learning and stimulation and caregiver-perpetrated violence, under fixed sample size constraints. MDES estimates will be based on a multilevel Poisson/negative binomial and a linear regression framework.

**3. Intervention Effect Estimation**

The primary evaluation of intervention effects will be conducted at the post-intervention timepoint (T1).

**3.1 Continuous Outcomes**

Continuous outcomes will be analyzed using multilevel linear regression models.

- **Model Specification:**
  - **Random Effects:** Participant ID nested within cluster.
  - **Fixed Effects:** Group (intervention vs. control), time (T0, T1, T2, T3), and the group × time interaction term. The intervention effect will be determined by the interaction term.

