**3.2 Frequency-Based Outcomes**

Frequency-based outcomes, such as caregiver-perpetrated violence, will be analyzed using either Poisson or negative binomial regression models. The choice of model will be determined by the presence of overdispersion in the data.

- **Model Specification:** The model structure will be identical to that described in section 3.1, including random and fixed effects.

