**7. Relationship to Trial Protocol and Statement of Deviation**

This Statistical Analysis Plan (SAP) serves as a detailed and specific elaboration of the data analysis principles outlined in the original trial protocol. The protocol provided a high-level summary of the analytical intentions, such as adhering to the intent-to-treat principle and conducting between-group comparisons.

This SAP operationalizes those intentions by pre-specifying the exact statistical models, covariates, and analytical methods to be used. Key specifications in this SAP that expand upon the protocol include the use of mixed-effects models to appropriately account for the clustered data structure and the precise definition of moderation and CACE analyses.

There are no deviations from the core aims or analytical principles described in the original trial protocol.

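### If clusters were allocated, the Section 3.1 model puts no cluster-level variance on the group × time effect, so the primary test holds 5% only if cluster means do not drift differently from T0 to T1

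*SAP*

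**What the plan says.** - **Section 3** sets the primary comparison: "The primary evaluation of intervention effects will be conducted at the post-intervention timepoint (T1").
- **Section 3.1** models continuous outcomes with fixed group, time and group × time, reads the effect from the interaction, and lists the random effects as "Participant ID nested within cluster". It names no cluster × time effect and no cluster-level slope.
- **Section 3.2** carries this over to counts: "The model structure will be identical to that described in section 3.1, including random and fixed effects".
- **Section 2** plans on clusters: "power calculations will assume 21 clusters, each comprising 20–35 participants (four discrete values"), with "intra-cluster correlation coefficients (ICCs) ranging from 0.01 to 0.05 (five values").
- **Section 1** sets the threshold: "a p-value of < 0.05 will be considered statistically significant for all analyses".
- **Section 7** lists among the SAP's additions to the protocol "the use of mixed-effects models to appropriately account for the clustered data structure".

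Two things are not stated. Section 3.1 does not call its random effects intercepts; that is the ordinary reading, and Section 6 describes random intercepts for clusters and participants in the complier analysis. The unit of randomisation is given nowhere in the SAP. Nor does the SAP give a robust variance or a rule for degrees of freedom.

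**The concern.** The tested quantity is a difference between arms in change over time. A cluster intercept that is constant over time adds the same amount to a cluster's T0 and T1 values and drops out of the change, and so does the participant intercept. What remains is residual variance, which the model treats as independent between participants of the same cluster.

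If whole clusters were allocated and some improved or worsened more than others for reasons unrelated to the intervention, the participants of a cluster share that movement. The fixed time effect removes only drift common to all clusters. The cluster-specific part goes into the residual, where it is averaged over several hundred participants instead of over 21 clusters. The standard error of the interaction is then too small and its p-value too low, on the comparison that the SAP makes primary. The presence of a cluster term in the model can hide this, because that term protects comparisons of level and not comparisons of change.

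**Working it through.** The SAP reports no power, sample-size or detectable-effect result to reproduce. The only figure to check against is the 0.05 threshold, taken as two-sided.

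**Inputs from the SAP:** 21 clusters; m = 20 to 35 per cluster (20, 25, 30 and 35 taken as the four values); ICC = 0.01 to 0.05, read as the ICC of the outcome.

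**Assumed, not in the SAP:** allocation by cluster, 11 vs 10; cluster autocorrelation (CAC) 0.8 to 1; individual autocorrelation (r) 0.5 and 0.7.

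**Step 1: does cluster variance enter the standard error?** A mixed model with cluster and participant intercepts was fitted to balanced simulated T0–T1 data. The interaction's standard error was 0.07038. The standard error from treating participants' change scores as independent was also 0.07038. Cluster variance does not enter.

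**Step 2: inflation of the variance.** With total outcome variance 1, write
- s_ct = ICC × (1 − CAC), the cluster-by-time variance;
- s_e = (1 − ICC) × (1 − r), the residual variance.

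Variance of a cluster's mean change: the model uses 2(s_ct + s_e)/m; the true value is 2(s_ct + s_e/m). The ratio is

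inflation = (m × s_ct + s_e)/(s_ct + s_e), and actual alpha = 2[1 − Φ(1.96/√inflation)].

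*Lower end (m = 20, ICC 0.01, CAC 0.95, r 0.5):* s_ct = 0.0005, s_e = 0.495; inflation = 0.505/0.4955 = 1.02; alpha = 5.2%.

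*Upper end at r 0.5 (m = 35, ICC 0.05, CAC 0.8):* s_ct = 0.01, s_e = 0.475; inflation = 0.825/0.485 = 1.70; alpha = 13.3%.

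*Same with r 0.7:* s_e = 0.285; inflation = 0.635/0.295 = 2.15; alpha = 18.2%.

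Over the SAP's whole range of m and ICC:

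| CAC | alpha, r = 0.5 | alpha, r = 0.7 |
|---|---|---|
| 1.0 | 5.0% | 5.0% |
| 0.95 | 5.2–7.1% | 5.4–8.5% |
| 0.9 | 5.4–9.2% | 5.7–12.0% |
| 0.8 | 5.9–13.3% | 6.5–18.2% |

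**Step 3: simulation** (5,000 runs per scenario, r 0.5), testing change with participants treated as independent:

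| m | ICC | CAC | T0–T1 data | T0–T3 data |
|---|---|---|---|---|
| 20 | 0.01 | 0.8 | 6.0% | 5.9% |
| 35 | 0.05 | 0.8 | 13.1% | 13.6% |
| 35 | 0.05 | 1.0 | 5.0% | 5.3% |

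A smaller run of 300 fitted mixed models at m = 35, ICC 0.05, CAC 0.8 rejected in 17% (Monte Carlo standard error about 2 points), of the same order.

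**Step 4: if individuals were randomised within clusters**, simulation gave 5.1% to 5.3%.

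**Step 5: after a repair.** A t-test on cluster mean changes with 21 − 2 = 19 degrees of freedom rejected in 4.4% to 5.7% across all eight simulated scenarios, including 4.9% where the Section 3.1 structure gave 13.1%.

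**Step 6: reference distribution.** Even with the correct variance, a normal reference on 21 clusters would give P(|t19| > 1.96) = 6.5%. The SAP names no reference, so this only illustrates why one should be fixed. It is not a further amount to add to the figures above.

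**The case against.** The strongest reply is that inflation needs two conditions that the SAP does not state.

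**Allocation by cluster.** ICCs also appear in the planning of trials that randomise individuals within clusters. Section 2 speaks of participants per group, Section 6 only of random assignment, and the protocol that would normally name the unit is not at hand. This stands: under individual randomisation there is no material inflation. The number of clusters and the ICC grid make cluster allocation the more natural reading, but it remains an inference.

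**Differential drift.** Nothing in the SAP shows or quantifies it, and at CAC 1 the rate is exactly 5%. This also stands as to size. It does not rescue the specification, which rests on zero cluster-by-time variance without saying so or giving a reason.

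A reader might infer that the primary false-positive rate certainly exceeds 5%, or that it is 7–23% because the plan's own ICCs imply it. The documents do not support either. From m = 20 with ICC 0.01 (1 + 19 × 0.01 = 1.19, alpha 7.2%) to m = 35 with ICC 0.05 (1 + 34 × 0.05 = 2.70, alpha 23.3%), that range treats 0.01–0.05 as ICCs of *change*. Section 2 does not present them so. The two kinds of ICC coincide only when CAC equals r, for example both 0.5, which is well below the CAC values used here.

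The count models are also open to question: they share the structure, but the exact equality of standard errors and all the simulations concern balanced continuous data.

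**Conclusion.** The point holds in conditional form. If clusters were allocated, the Section 3.1 model with intercepts only gives the group × time effect no cluster-level variance, and Section 7's statement is true of that parameter only when cluster means do not drift differently between T0 and T1.

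For continuous outcomes the size runs from none (CAC 1) to 13.3% at r 0.5 or 18.2% at r 0.7 (CAC 0.8). In standard-error terms the understatement at r 0.5 and CAC 0.8–0.95 is a factor of √1.02 = 1.01 to √1.70 = 1.30. CAC, r and the 11 vs 10 split are assumptions. For counts the same weakness is to be expected from the shared structure, but its size is not established.

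This is a fault in a stated primary model and not merely a missing detail: as written, it can yield a wrong p-value. How much it matters turns on the unit of allocation, which the sponsor can settle at once.

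**What to change.** 1. State the unit of allocation in the SAP.
2. If it is the cluster, change the primary model in one of two ways: add a random cluster × time effect to the T0–T1 comparison, or model T1 with baseline as a covariate and a cluster random intercept.
3. Fix small-sample degrees of freedom based on clusters: Kenward-Roger or Satterthwaite for continuous outcomes (about 19). For counts, use a t reference on clusters minus 2 or a cluster permutation test.
4. Add the cluster × time term to the time contrasts in Section 5, which uses the same random effects. Degrees of freedom there should rest on the number of intervention-arm clusters, which the SAP does not give.
5. Reword Section 7 so that its claim matches the revised model.

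The cost is SAP wording and small changes to code. Confidence intervals will be somewhat wider, and correctly so if clusters drift. If individuals were randomised within clusters, stating that is enough for the primary test.

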**3.3 Sensitivity Analyses**

To assess the robustness of the findings, sensitivity analyses will be conducted by adjusting the primary models for a set of pre-specified covariates.

- **Covariates:** Child age, child gender, caregiver age, and caregiver gender.

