**5. Follow-up Analysis in the Intervention Group**

Due to the waitlist control design, the control group began receiving the intervention after the post-intervention (T1) assessment. Therefore, between-group comparisons at the 6-month (T2) and 12-month (T3) follow-ups are not possible.

- **Method:** Analyses will be restricted to the intervention group data.
- **Generalized linear mixed-effects models** will be applied, using baseline (T0) as the reference point.
- **Model Specification:**
  - **Random Effect:** Participant ID nested within cluster.
  - **Fixed Effect:** Time (T1, T2, T3) will be included as a fixed effect to assess changes in outcomes from baseline.

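### The primary T1 effect for continuous outcomes is a change-score contrast: unbiased, but less precise under random assignment than an analysis that uses the collected baseline

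*SAP*

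**What the plan says.** SAP section 3 sets T1 as the time at which the effect is primarily judged. Section 3.1 lists the fixed effects as "Group (intervention vs. control), time (T0, T1, T2, T3), and the group × time interaction term" and the random effects as "Participant ID nested within cluster", and adds that "The intervention effect will be determined by the interaction term". With four time levels there are three interaction coefficients. Section 3.1 does not name one, but read with section 3 it must be the T1 coefficient relative to T0.

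Section 3.2 carries this over to count outcomes: "The model structure will be identical to that described in section 3.1, including random and fixed effects". The only covariate adjustment is the sensitivity analysis in section 3.3, on "Child age, child gender, caregiver age, and caregiver gender". The baseline value of the outcome is a covariate nowhere, and the groups are nowhere given a common T0 mean. Baseline is collected: section 5 describes its models as "using baseline (T0) as the reference point". Section 6 relies on random assignment as its instrument.

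On size, section 2 says that "the sample size is primarily determined by real-world logistical constraints". It plans MDES calculations over 21 clusters, 20–35 participants per cluster and ICCs from 0.01 to 0.05.

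**The concern.** Including a group main effect makes the model estimate a separate T0 mean in each group and subtract the difference. Under random assignment the true T0 means are equal, so the model spends information on a parameter known to be zero, and the noise in the observed T0 difference passes in full into the effect estimate. An analysis that uses the baseline subtracts only the share of that difference that predicts T1.

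What is at stake is precision, not validity. Because logistics fix the sample, recruitment cannot make up the loss, whereas the analysis can with data already planned. The variance of the planned contrast also depends directly on the T0–T1 correlation, which is not among the power inputs listed in section 2.

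**Working it through.** The SAP states no power, MDES, effect size or SD, so there is no figure of its own to reproduce.

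**Inputs from the SAP:** 21 clusters; m = 20–35 per cluster; ICC 0.01–0.05; significance at 0.05; random intercepts for cluster and participant.

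**Assumed, because not given:** T0–T1 correlation within a participant rho = 0.3, 0.5, 0.7; two-sided test; 80% power; complete data; total variance 1 at each wave; and either clusters randomised 10/11 or individuals randomised 1:1 within clusters.

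**Step 1: what the interaction estimates.** In simulated complete data with four waves, the group × T1 coefficient from the section 3.1 model was 0.19458, and the difference in mean T1 − T0 change was 0.19458. Dropping T2 and T3 left the standard error unchanged (0.0977 at m = 20, rho = 0.5, clusters randomised), so the later waves recover nothing.

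**Step 2: individuals randomised.** The variance is proportional to 2(1 − rho) for the change contrast and to 1 − rho² when baseline is used. The ratio is (1 + rho)/2, so the reduction is (1 − rho)/2.

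- rho 0.3: 1.40 against 0.91, ratio 0.65
- rho 0.5: 1.00 against 0.75, ratio 0.75
- rho 0.7: 0.60 against 0.51, ratio 0.85

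Exact generalised least squares with the cluster intercept included gives 0.63–0.65, 0.74–0.75 and 0.84–0.85.

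**Step 3: clusters randomised.** The cluster intercept already cancels in the change contrast, so there is less to gain. Let D = 1 + (m − 1) × ICC. The correlation between a cluster's T0 and T1 means is r = [rho + (m − 1) × ICC]/D, and the ratio of baseline-using to planned variance is (1 + r)/2 = 1 − (1 − rho)/(2D).

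| m | ICC | D | rho 0.3 | rho 0.5 | rho 0.7 |
|---|---|---|---|---|---|
| 20 | 0.01 | 1.19 | 0.706 | 0.790 | 0.874 |
| 20 | 0.05 | 1.95 | 0.821 | 0.872 | 0.923 |
| 35 | 0.01 | 1.34 | 0.739 | 0.813 | 0.888 |
| 35 | 0.05 | 2.70 | 0.870 | 0.907 | 0.944 |

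Exact generalised least squares gives the same values. The variance reductions are therefore 13–29%, 9–21% and 6–13%. Taking square roots, the standard error falls by 7–16%, 5–11% and 3–7%.

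**Step 4: MDES example, clusters randomised, m = 20, rho = 0.5.**

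- Planned SE = √[2(1 − 0.5)/20 × (1/10 + 1/11)] = √0.009545 = 0.0977
- MDES = (1.960 + 0.842) × 0.0977 = 0.274 SD
- Using baseline, ICC 0.01: SE = 0.0977 × √0.790 = 0.0868, MDES 0.243 SD
- Using baseline, ICC 0.05: SE = 0.0977 × √0.872 = 0.0912, MDES 0.256 SD

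These use the normal approximation.

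**The case against.** The best defence is that group, time and group × time with random intercepts is a standard, unbiased longitudinal analysis. It keeps every participant with any measurement, which suits the intention-to-treat commitment in section 1, and choosing it over a more efficient model could be called preference. The loss depends on a correlation that the documents do not give, and in the least favourable cell (clusters of 35, ICC 0.05, rho 0.7) the standard error falls by only 3%. All of this stands, and it limits the point to efficiency. It does not remove the point, because a model with a common T0 mean keeps the same participants and gains in every cell examined.

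Four stronger readings are tempting but not supported:

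- **That the planned contrast is worse than ignoring baseline when rho is below 0.5.** This needs individual randomisation, and the SAP does not state the unit. If clusters were randomised, the variance ratio of the change contrast to a T1-only comparison is 2(1 − rho)/D. At rho 0.3 this runs from 1.4/2.70 = 0.52 to 1.4/1.19 = 1.18. Over sizes 20, 25, 30 and 35 and ICCs 0.01 to 0.05, the planned contrast is the more precise in 15 of 20 cells.
- **That the variance reductions translate into a set number of participants saved.** Under cluster randomisation the reduction itself changes with cluster size and ICC, so no single conversion holds.
- **That the same figures apply to caregiver-perpetrated violence.** For counts the interaction is a ratio of rate ratios, and the linear variance formula does not carry over exactly. No gain has been calculated there.
- **That the planned MDES is wrong.** Section 2 describes calculations still to be done and also omits SD and power, so its list of inputs may be incomplete. What can be said is that the correlation needs to be stated.

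**Conclusion.** The point holds as a loss of efficiency for continuous outcomes; it is neither bias nor invalidity. Over the assumed correlations of 0.3 to 0.7, the avoidable variance is about 15–35% if individuals were randomised and about 6–29% over the SAP's own planning grid if clusters were. The direction is certain for any correlation below 1; the size depends on a correlation and a unit of randomisation that the SAP does not give.

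The figures also rest on complete data (with missing waves the estimate becomes a weighted version of the change contrast) and on a cluster effect that is constant over time. If cluster effects correlate 0.8 between waves instead, the cluster-randomised ratios become 0.69–0.81, 0.77–0.84 and 0.86–0.88, a somewhat larger gain. The argument further requires T0 to be comparable between groups by randomisation; a chance difference in the observed T0 means does not breach that.

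**What to change.** Preferred: for the primary continuous-outcome analysis, keep T0 and T1 as outcome waves with the cluster and participant random intercepts, drop the group main effect, and keep the group × T1 term, so that both groups share a T0 mean. State that this coefficient is the primary effect. Participants with only one wave remain in the analysis.

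Alternative: regress the T1 outcome on group and the T0 outcome, with a cluster random intercept. This is not equivalent when waves are missing, because it drops anyone without T0 or T1. If the cluster mean of the baseline is added as well, it uses a cluster-level degree of freedom out of 21 clusters.

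State the unit of randomisation, and base the continuous-outcome MDES on whichever model is chosen, with a stated range for the T0–T1 correlation. The section 3.1 model can be kept as a sensitivity analysis. The cost is SAP wording and a rerun of the MDES calculation; no new data are needed.
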